### Secondary outcome measurements

#### VAS

The intensity of pain in the cervical region is measured with a 10-cm VAS, for which 0 means “absence of pain,” while 10 represent “the worst pain imaginable.” The patients will be asked: “How much pain do you have at this moment?” To extract the data, the researcher measures the distance between the start of the scale (absence of pain) and the mark set by the participant. The VAS will be assessed using a repeated longitudinal analysis. The VAS has been shown to be a valid and reliable outcome measure [21–23] and the test–retest reliability has proven to be good (intraclass correlation 0.92) [24].

#### NDI

The change in neck function will be evaluated using the NDI, which is the most frequently used questionnaire to evaluate cervical pain and functional limitations in daily life. It consists of 10 questions about pain intensity, personal care, lifting, reading, headaches, concentration, work, sleeping, driving, and recreation. Each question is answered on a scale from 0 to 5. The total score ranges from 0 to 50 points, with higher scores indicating more severe symptoms. At least 8 of the 10 sections must be answered for the score to be calculated. The NDI is reliable and valid [25–28]. The NDI will be assessed using a repeated longitudinal analysis.

#### SF-36

The SF-36 questionnaire assess the correlation between health-related quality of life and various factors [29, 30]. It consists of 36 questions grouped in 8 domains: vitality (4 items), physical functioning (10 items), bodily pain (2 items), general health (5 items), physical role (4 items), emotional role (3 items), social functioning (3 items), and mental health (5 items). For each domain, scores range from 0 to 100 and higher scores reflect a better quality of life. The SF-36 will be assessed using a repeated longitudinal analysis.

### Safety evaluation

At each visit, researchers will evaluate adverse events (AEs), which are defined as unexpected or unfavorable responses that occur during or after treatment. In this trial, AEs are defined as events that (1) lead to hospitalization, (2) prolong a department (Outpatient department or inpatient wards) or hospital stay, (3) cause a disability, (4) hinder ability to work, or (5) are a threat to life. For any AE, regardless of whether it is related to the interventions, treatment should be terminated immediately. The patient should receive any remedial treatment and the AE will be reported to the relevant responsible units and ethical committees to determine whether the patient should drop out of the trial. All patients with an AE will be followed up until the event has been resolved or the patient’s condition has become chronic or stable.

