### Dropout criteria

Participants who do not complete the clinical protocol for the following reasons should be considered as dropped out:The patient quits (poor efficacy or adverse reactions)Loss to follow-upResearchers remove the patient (poor compliance, complications, or serious adverse events)

The trial communicator will communicate in-depth with patients who want to withdraw from the trial because of poor efficacy or have no time to promote retention.

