### Follow-up

To evaluate the short-term efficacy, long-term efficacy, and the safety of the interventions, we will follow up participants for 3 months after the trial. During the 3 months of unsupervised follow-up, no participants will undergo special therapy with the exception of routine cervical care. At weeks 10 and 16, the outcome assessor will telephone participants to investigate the recurrence of their neck pain. Patients can also inform the assessors of their clinical symptoms and AEs face to face or by email, text message, or WeChat at the relevant time points.

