### Data collecting and monitoring

Demographic and baseline characteristic data will be collected by screeners when the patients are recruited. Clinical outcomes, questionnaire-based assessment of treatment effects and neck physiological function, and details of adverse events will be recorded by outcome assessors in case report forms (CRFs). Completed CRFs are reviewed by a four-person steering committee, which is composed of the principals of the four research centers, and submitted to the data administrators, who are independent from the research team and blinded to group allocation, for data entry and management using an Excel database. All data administrators have data analysis qualifications and are trained uniformly. To ensure the accuracy of the data, two data administrators independently enter the information and proofread it. If there are issues with the information in the CRF, the data administrators can fill out a query sheet and give it to the steering committee. The data administrators can then modify the data according to any revisions made by the steering committee. After confirming that the database is correct, the steering committee, data administrators, and statistician will lock the database.

This trial uses an electronic data management system. The system integrates electronic CRFs, data entry, data locking, data exporting, and system contingency plans, which enable scientific tracking and real-time monitoring of the test data.

The Department of Science and Technology in Yueyang Hospital, which is not taking part in the study, will be responsible for monitoring the data. The CRFs, protocol compliance, data management, treatment administration, and AEs will be monitored independently during the study.

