### Statistical analyses

The analysis set will consist of a full analysis set (FAS), a per protocol set, and a safety set. The safety set will include any participants who were randomly assigned and received at least one massage treatment. The FAS will include data indicating that the treatment was as close to intention to treat as possible. In addition to meeting the criteria of the safety set, to be included in the FAS, the participants must have been evaluated for the primary outcome at least once. To be included in the per protocol set, participants must receive more than nine sessions of treatment (75%). The FAS will be used in the main analysis. For missing data, we will analyze the underlying reason and use an imputation adjustment approach, and the last observation carried forward analysis will be used to handle the missing data. After the main analysis, a sensitivity analysis will be performed by comparing the results from the per protocol analysis and the intention to treat analysis to evaluate the impact of missing data on the trial results.

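### The Safety evaluation section gives two conflicting definitions of an adverse event, and neither works with the stop-treatment rule that follows

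*Protocol article*

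**What the plan says.** In the protocol article, the Safety evaluation section opens by saying that researchers will evaluate AEs at each visit, "which are defined as unexpected or unfavorable responses that occur during or after treatment". No severity threshold is attached.

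The next sentence begins a second definition: "In this trial, AEs are defined as events that (1) lead to hospitalization". Four further criteria follow: a prolonged stay (the text names outpatient department, inpatient ward and hospital), disability, hindered ability to work, and threat to life.

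The section then sets the action: "For any AE, regardless of whether it is related to the interventions, treatment should be terminated immediately". Responsible units and ethics committees are told, and it is then decided whether the patient drops out.

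Other sections use related terms:

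- Dropout criteria: a patient may quit because of "poor efficacy or adverse reactions", while researchers may "remove the patient (poor compliance, complications, or serious adverse events".
- Data collecting and monitoring: "details of adverse events will be recorded by outcome assessors in case report forms (CRFs".
- Follow-up: "Patients can also inform the assessors of their clinical symptoms and AEs face to face", or by several remote channels.
- Statistical analyses: "The safety set will include any participants who were randomly assigned and received at least one massage treatment". Adverse effects are summarised as counts and percentages and compared between groups by a chi-squared or Fisher's exact test.

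**The concern.** The two definitions classify the same event differently, and everything downstream (recording, stopping treatment, ethics reporting, the comparison between groups) depends on which one a site applies. The five-item list reads largely as a list of seriousness criteria attached to the wrong label.

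This matters because the Discussion describes the trial as a study of comparative safety as well as effectiveness, and the Abstract promises a safety evaluation after every session. The arms differ in a component with its own potential for reactions: the tuina arm receives a structural adjustment of the neck with stretching, traction and twisting (Step two: neck structural rectification), and the Discussion says that the control massage has no joint adjustment. If milder reactions are recorded unevenly or not at all, a difference between the arms on that component could be missed. A reaction not noted at the session is hard to recover later.

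**Working it through.** The plan has no figure to reproduce. The check is to apply each definition to the same events and follow the consequences.

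| Event after a session | First sentence | Five-item list |
|---|---|---|
| Hospitalization, disability, threat to life | AE | AE |
| Reaction that hinders work | AE | AE, item 4 |
| Dizziness that keeps the patient longer in the outpatient department | AE | Arguably AE, item 2 |
| Bruising or a brief pain flare, no longer stay, work not hindered | AE | Not an AE |

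The last row is the conflict. Each way of reading the section then has a cost.

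1. **The list governs.** The words that limit it to this trial favor this reading. So does the stop rule, which is workable only if AEs are fairly grave. The reactions in the last row then fall outside the AE category. The CRF sentence in Data collecting and monitoring speaks of AEs, so nothing shown obliges a site to record them, and they may not reach the comparison between groups.

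2. **The broad sentence governs.** It is not withdrawn, and it is the one tied to evaluation at each visit. The stop rule then applies to any unfavorable response, whether related to treatment or not. That is hard to operate where the tuina force is set by a sensation described as dull pain, numbness or soreness (Step one: local manipulation). It could also cost participants their place in the per protocol set, which requires more than nine of the 12 sessions, if treatment is not resumed.

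3. **Sites differ.** With four centers and two definitions, AE counts may not be comparable across centers.

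The Dropout criteria point to the likely intention. They separate adverse reactions, which may lead a patient to quit, from serious adverse events, which lead researchers to remove the patient. Two levels are meant, and the five items fit the second better than the first.

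Other data cover the gap only in part. The VAS records current pain, the NDI includes pain and headaches, and the NPQ covers pain and numbness. They are completed at set weeks as efficacy scores, not as events after a session. As described, none lists bruising. Reporting by patients under Follow-up is optional and comes after treatment has ended.

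**The case against.** The best counter-case is that this is a labelling slip. The broad sentence still stands, so sites may record everything. The statistical section speaks of adverse effects and does not tie them to the five items. A journal article does not set out the whole CRF. The definition also applies equally to both arms, and control patients receive manual treatment to which they can react too.

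Much of this stands, and it rules out several stronger readings that a reader might infer:

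- **That mild reactions will certainly be lost.** The text supports only that they may be, because either definition could be applied.
- **That four of the five items are strictly seriousness criteria and only hindered work goes wider.** The stay criterion names the outpatient department, so a patient kept back in the clinic after a session may qualify.
- **That AEs are the only safety item on the CRF, or that the trial has no SAE definition at all.** The full protocol may contain more, so neither is part of this point.
- **That exposure measures the damage.** Up to 178 × 12 = 2,136 planned tuina sessions include the adjustment. That counts exposure, not unrecorded events.

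The conflict itself survives. Condensing a protocol explains missing detail. It does not explain two incompatible definitions in consecutive sentences, followed by a mandatory action that depends on which one is meant.

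**Conclusion.** The point holds as an inconsistency with practical consequences for safety data, and it should be fixed. Under one reading, reactions that neither prolong a stay nor hinder work may go unrecorded. Under the other, treatment must stop for trivial events. If centers differ, the counts are inconsistent. Any of these weakens the comparison of safety between arms, including for the adjustment that only the tuina arm receives.

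The size cannot be computed, because the article gives no reaction rates and none are assumed here. The conclusion rests on the wording of the Safety evaluation section and on the assumption that sites work from that wording. Neither the primary analysis nor the sample size uses the AE definition, so both are unaffected.

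**What to change.** 1. Keep the first sentence of Safety evaluation as the AE definition. Record AEs at each session, whatever their severity or relation to treatment.
2. Relabel the five criteria as the definition of a serious adverse event, the term that the Dropout criteria already use.
3. Limit mandatory immediate termination and ethics committee reporting to SAEs or events that make further treatment unsafe. Without this step, the broader AE definition would stop treatment for trivial reactions.
4. Report AEs and SAEs by arm in the safety set.

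The cost is a change of wording, one seriousness field on the CRF, and slightly more recording at visits that already take place. The sample size and the primary analysis stay as they are.

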### Follow-up

To evaluate the short-term efficacy, long-term efficacy, and the safety of the interventions, we will follow up participants for 3 months after the trial. During the 3 months of unsupervised follow-up, no participants will undergo special therapy with the exception of routine cervical care. At weeks 10 and 16, the outcome assessor will telephone participants to investigate the recurrence of their neck pain. Patients can also inform the assessors of their clinical symptoms and AEs face to face or by email, text message, or WeChat at the relevant time points.

### Blinding test and credibility test

Questionnaires on blinding will be completed at weeks 2, 4, 10, and 16. The success of these blinding strategies will be appraised at the end of the study. The credibility rating for both treatments will be evaluated using a credibility test at week 2 and at the end of the treatment with a seven-point scale developed by Vincent et al. The participants will rate the scores (0 = very low confidence and 6 = very high confidence) for the following four questions:How confident do you feel that this treatment can alleviate your chronic neck pain?How confident would you be in recommending this treatment to a friend who suffered from a similar complaint?How logical does this treatment seem to you?In your opinion, how successful could this treatment be in alleviating other complaints?

### Data collecting and monitoring

Demographic and baseline characteristic data will be collected by screeners when the patients are recruited. Clinical outcomes, questionnaire-based assessment of treatment effects and neck physiological function, and details of adverse events will be recorded by outcome assessors in case report forms (CRFs). Completed CRFs are reviewed by a four-person steering committee, which is composed of the principals of the four research centers, and submitted to the data administrators, who are independent from the research team and blinded to group allocation, for data entry and management using an Excel database. All data administrators have data analysis qualifications and are trained uniformly. To ensure the accuracy of the data, two data administrators independently enter the information and proofread it. If there are issues with the information in the CRF, the data administrators can fill out a query sheet and give it to the steering committee. The data administrators can then modify the data according to any revisions made by the steering committee. After confirming that the database is correct, the steering committee, data administrators, and statistician will lock the database.

This trial uses an electronic data management system. The system integrates electronic CRFs, data entry, data locking, data exporting, and system contingency plans, which enable scientific tracking and real-time monitoring of the test data.

The Department of Science and Technology in Yueyang Hospital, which is not taking part in the study, will be responsible for monitoring the data. The CRFs, protocol compliance, data management, treatment administration, and AEs will be monitored independently during the study.

### Statistical analyses

The analysis set will consist of a full analysis set (FAS), a per protocol set, and a safety set. The safety set will include any participants who were randomly assigned and received at least one massage treatment. The FAS will include data indicating that the treatment was as close to intention to treat as possible. In addition to meeting the criteria of the safety set, to be included in the FAS, the participants must have been evaluated for the primary outcome at least once. To be included in the per protocol set, participants must receive more than nine sessions of treatment (75%). The FAS will be used in the main analysis. For missing data, we will analyze the underlying reason and use an imputation adjustment approach, and the last observation carried forward analysis will be used to handle the missing data. After the main analysis, a sensitivity analysis will be performed by comparing the results from the per protocol analysis and the intention to treat analysis to evaluate the impact of missing data on the trial results.

Data normality will be tested through visual inspection of histograms. According to the results of the homogeneity and normality analysis, parametric statistics (Tukey test) or non-parametric statistics (Wilcoxon rank sum test) will be used for the within- and between-group analyses. Descriptive statistics will be used to compare demographic and baseline information and to evaluate the credibility of the groups. If an adjustment for possible baseline incomparability is needed, a covariance analysis will be performed. Efficacy is measured at five time points. Therefore, a repeated measures analysis of variance will be used to investigate the effect of treatment, time, and interaction terms between treatment groups versus time. Two-sided paired *t* tests will use within-group comparisons (comparing baseline to follow-up). A chi-squared test or a Fisher’s exact test will be performed to determine categorical variables between groups and adverse effects, which will be recorded and described as a frequency and percentage. Fisher’s exact test will be used if a cell has an expected value of less than 5 that is equal to or more than 20%. All statistical analyses will be performed with the Statistical Package for Social Sciences (SPSS, version 21.0, SPSS Inc., Chicago, IL, USA) by statisticians who are independent of the research team and blinded to the group allocation. The confidence interval will be established at 95%, and the significance level at 0.05.

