### Sample size calculation

The expected efficacy rate of the *tuina* group measured by the NPQ is 95%. According to the literature, the efficacy rate for traditional Chinese massage is 85%. The sample size was calculated with a significance level of 0.05 and power of 0.80. According to the calculation in SPSS, the required sample size was 320. With a maximum dropout tolerance of 10%, 356 patients are needed for the trial, with 178 for each group across the four centers.

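### Missing outcomes are carried forward in the main analysis, and the one missing-data check named does not vary that assumption

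*Protocol article*

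**What the plan says.** All references are to the protocol article.

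- **Statistical analyses.** The FAS is the main analysis set. A patient enters it after at least one treatment and at least one evaluation of the primary outcome. On missing values the section says: "For missing data, we will analyze the underlying reason and use an imputation adjustment approach", and then that "the last observation carried forward analysis will be used to handle the missing data". The sensitivity analysis consists of "comparing the results from the per protocol analysis and the intention to treat analysis to evaluate the impact of missing data on the trial results". The per-protocol set is defined by treatment sessions received (more than nine). The longitudinal method is repeated measures analysis of variance.
- **Dropout criteria.** Three routes are listed: "The patient quits (poor efficacy or adverse reactions"), loss to follow-up, and removal by the researchers for poor compliance, complications or serious adverse events.
- **Interventions; Follow-up.** Neck function is assessed at baseline and at weeks 2, 4, 10 and 16. At weeks 10 and 16 "the outcome assessor will telephone participants to investigate the recurrence of their neck pain".
- **Primary outcome measurement; Sample size calculation.** Success is an improvement of more than 30% on the Northwick Park questionnaire (NPQ). The planning rates are 95% for tuina and 85% for traditional Chinese massage, with 10% dropout allowed for.

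**The concern.** Carrying a value forward makes two different assumptions in this schedule. For a patient who leaves during treatment, it freezes a mid-treatment score and assumes no further change up to week 4. For a patient lost after treatment, it carries the end-of-treatment score to weeks 10 and 16 and assumes no relapse, although recurrence is what those contacts are meant to detect. In both cases the filled-in value enters the analysis as if measured, so uncertainty is understated.

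Some of the stated dropout reasons are tied to how the patient is doing, so those who leave may differ from those who stay. If the arms lose patients at different rates or times, the carried values can create or hide a difference between them.

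A sensitivity analysis should reveal this. The one named has that aim, but what it changes is which patients are analysed, by adherence. It does not change what is assumed about unobserved outcomes.

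**Working it through.** **1. The plan's own figures.** With p1 = 0.95, p2 = 0.85, two-sided alpha 0.05 (sidedness is not stated, so this is assumed) and power 0.80, the pooled two-proportion formula gives 141 per arm. With the continuity correction it gives 160 per arm, or 320 in total. Then 320 / 0.90 = 355.6, rounded up to 356. Both stated figures reproduce. The target difference is 10 points, and the dropout allowance is 356 - 320 = 36 patients.

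**2. Gap created by carrying values forward when there is no true difference.** Let p be the true success rate at the analysed visit (the same in both arms, and the same for dropouts and completers), w the success rate of the carried value, and dT and dC the dropout in the tuina and massage arms. The expected rate in each arm is (1 - d)p + d·w, so

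gap = (dC - dT)(p - w).

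Assumptions, none from the protocol: p = 0.85; dT = 0.05 and dC = 0.15, all after week 2; w = 0.40 to 0.60 at week 2. The analysed visit is week 4, for illustration only, since the article fixes no single primary visit.

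| w | Tuina | Massage | False gap |
|---|---|---|---|
| 0.40 | 0.95×0.85 + 0.05×0.40 = 0.8275 | 0.85×0.85 + 0.15×0.40 = 0.7825 | 4.5 points |
| 0.50 | 0.8325 | 0.7975 | 3.5 points |
| 0.60 | 0.8375 | 0.8125 | 2.5 points |

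At 178 per arm, a nominal 5% test of these rates rejects about 10% (w = 0.60) to 19% (w = 0.40) of the time.

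- Reversed imbalance (15% tuina, 5% massage): the same size against tuina, -2.5 to -4.5 points.
- Milder imbalance (8% versus 12%) with w = 0.40: 0.04 × 0.45 = 1.8 points.
- Equal dropout: (dC - dT) = 0, so no false gap.
- Recurrence after week 4: at weeks 10 and 16 the carried value may be better than the truth (w > p). The sign flips, and the arm that loses more patients looks better.

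**3. Does the per-protocol comparison vary the assumption?** Consider three patients, taking intention to treat to mean the FAS.

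| Patient | FAS | Per-protocol | What the comparison shows |
|---|---|---|---|
| All 12 sessions, lost before week 10 | In, week 4 value carried | In, presumably the same value carried | Nothing: any error is the same in both |
| Few sessions, all outcomes recorded | In, nothing missing | Out | A change unrelated to missing data |
| Few sessions, then lost | In, early value carried | Out | Deletion by adherence, mixed with the effect of carrying forward |

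Only the third patient lets the two results diverge because of missing data, and even then the cause cannot be separated from adherence. In the step 2 scenario the early dropouts would leave the per-protocol set and the two results would differ, but a reader could not tell why. For losses after treatment the two results can agree while sharing the same error.

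**The case against.** The strongest reply has four parts.

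- **Carry-forward is not the only step stated.** The same sentence promises a review of reasons and an imputation approach, and a fuller analysis plan may spell these out. This stands in part: it would be wrong to say that missing data receive no other attention. But the article does fix carry-forward as its one named method and the per-protocol comparison as its one named check, and the objection is to those choices, not to missing detail.
- **Bias is possible, not certain.** A reader might infer that dropout bias necessarily enters the primary result. The document does not support that. Equal dropout with no true effect gives no false gap, and losses after week 4 do not affect a week 4 comparison. Loss to follow-up is listed separately from poor efficacy, lack of time is also mentioned, retention contact is planned, and nothing says that outcome collection stops at dropout. This stands in full.
- **The dropout split is hypothetical.** True. The protocol plans for 10% overall and gives no reason to expect 5% versus 15%. The figures show scale only.
- **Sample size.** A reader might infer that, because dropouts stay in the FAS, the stated power of 0.80 is not delivered. That does not follow. At 178 per arm with 10% dropout in each, uncorrected power is 0.58-0.75 if dropouts succeed at 0-70% identically in both arms. It is 0.79 if they succeed at 60% versus 50%, 0.82 at 70% versus 60%, and 0.885 at the planning rates. The answer depends wholly on the assumption chosen. The stated 320 and 356 reproduce exactly, and "With a maximum dropout tolerance of 10%, 356 patients are needed for the trial" reflects ordinary inflation for dropout.

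**Conclusion.** The concern holds in two limited statements. First, the only concrete missing-data rule for the main analysis assumes no change after dropout, which sits badly with the protocol's own dropout reasons and its follow-up for recurrence. It can bias the comparison towards either arm when dropout rate or timing differs. Under the assumptions above the false gap is 2.5-4.5 points, a quarter to just under half of the 10-point target; it is smaller under milder imbalance and zero under equal dropout with no true effect.

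Second, the check offered "to evaluate the impact of missing data on the trial results" does not serve that purpose. This needs no numerical assumption: it follows from a per-protocol set defined by sessions received. Missing data are not ignored, but they are not validly tested by the check named. No conclusion about power or sample size follows.

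**What to change.** 1. Remove last observation carried forward. Analyse the continuous scores with a likelihood-based mixed model for repeated measures on all observed visits.
2. For the success outcome (more than 30% improvement), multiply impute the NPQ score within arm from baseline and the observed visits, then derive success from the imputed scores.
3. Replace the per-protocol versus intention-to-treat check with analyses that vary the missing-data assumption. The main one should be delta-adjusted imputation: shift the imputed scores step by step in each arm and report where the conclusion changes. Coding all dropouts as failures should be an extreme case only. In the 5% versus 15% illustration it gives 0.95×0.85 - 0.85×0.85 = 8.5 points of false gap, more than carrying forward does.
4. Keep the per-protocol analysis, labelled as an adherence analysis.

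The cost is revised wording and some extra programming, with no new data. The article reports that recruitment is still under way, so the change can be made before database lock and unblinding. The mixed model and the imputation still assume that data are missing at random; the delta-adjusted analysis is there to probe that.
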